### 2.2. Study Design

A multicenter retrospective cross-sectional study will be conducted. A convenience sample of all patients admitted and discharged in the year 2022 will be collected. Data will be collected retrospectively from two sources: (1) hospital discharge records and (2) nursing records. Retrospective data collection will offer a comprehensive picture of the nursing care delivered, as well as the possible heterogeneity of information on nursing activities provided by various healthcare institutions. The discharge records will be used to extract patient demographic data (e.g., gender, residency) and clinical data (e.g., diagnosis, diagnostic procedures performed, and length of stay). Nursing care activities (i.e., frequency and type) will be collected from nursing records. These data will be extracted from the EHR systems of each participating hospital.

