### 2.8. Data Analysis

Descriptive statistics (frequency, percentage, mean, median, range, and standard deviation) will be used to describe the sample. *t*-tests, ANOVA (or related nonparametric tests in case of a non-normal distribution of dependent variables), linear regression, and quantile regression will be performed to evaluate the possible variability in nursing time across hospitals and DRGs.

The chi-square test will be used to analyze any differences in the average frequency of nursing activities within the same DRG. In addition, we will perform linear, logistic and quantile regression, considering cost as the outcome of nursing care. Nursing costs will be assessed across hospitals and DRGs. The quantile regression will be used to explore which factors are associated with the different quantiles of nursing costs.

Nursing costs will be calculated based on several factors, including the average time required to perform each procedure, nurses’ hourly wage, the cost of materials used, and the average length of patient stay. Nursing time will be estimated using a convenience sample of nurses from the hospitals included in this study. For each nursing activity, the participating nurses will indicate the average time spent on the activity and devices relevant to each intervention. Nursing costs will be calculated by applying nurses’ salaries, based on national cost tables for nursing professionals. The annual nursing salary will be used to estimate the cost per minute of nursing time. This cost per minute will then be multiplied by the amount of time spent on each nursing activity and by the total number of activities performed for each patient. Additionally, the cost of devices required to perform each activity will be included, based on prices from the national price list. Thus, the cost per patient per day of hospitalization will be calculated. This cost will enable us to compare patients with different lengths of stay. Finally, subgroups based on patient complexity will be considered.

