Moreover, nursing costs will also be compared between patients with chronic and acute diseases. This will allow us to explore the hidden nursing costs derived from the nursing care delivered on an ongoing basis for chronic diseases (e.g., symptom monitoring, administration of medication for the chronic disease, etc.) that did not show signs of exacerbation during hospitalization. A subgroup analysis will be considered to determine which patients require more nursing care (in terms of time and costs). The nursing case mix (i.e., the patient characteristics that best explain the amount and costs of nursing care) will be evaluated to provide evidence for separating out nursing care activities and nursing intensity in the Italian prospective payment system.

To enable accurate data analysis, the need to normalize scores obtained from different rating scales measuring the same outcome will be evaluated. If information from the retrieved nursing records is missing, a missing value analysis will be performed to assess the appropriateness of multiple imputation [21]. Specifically, the reason for missingness will be examined, followed by the analysis of fraction of missing information and assessment of auxiliary variables to be used for multiple imputation. Then, sensitivity analyses involving several imputation models may be performed based on missing value analysis. Patients with missing data from all variables retrieved from the nursing record (i.e., missing data on nursing activities, nursing assessment and patient complexity) will be excluded. All descriptive and inferential analyses will be performed using R V. 4.4.2 [22] or similar software. The level of significance for all analyses will be fixed at *p* < 0.05.

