### 2.9. Source of Bias

The potential sources of bias in this study will include selection bias due to the proposed convenience sample, which will consist of five public hospitals in Italy. However, we expect to collect a substantial amount of data from patients across all geographical areas of Italy, with an estimated sample size of at least 15,000 individuals. Data collection bias may also arise from retrospective data collection, where incomplete records could affect the results, leading to inconsistencies in estimating the amount of nursing activities digitally registered and the related nursing costs. This bias will be controlled by performing multiple data imputation. Contextual biases related to institutional policies and healthcare culture may also influence nursing practices and patient care across different hospitals. Therefore, a thorough examination of institutional policies and healthcare cultures will be required to address contextual biases during data analysis. A potential source of bias is that the estimated nursing costs are based on a convenience sample of nurse estimates. This approach may not accurately capture the variability in nursing care across different settings. As a result, there is a risk of either overestimating or underestimating nursing costs, depending on how accurately nurses report the time spent on various activities. Thus, the development of standardized data collection guidelines, and the provision of comprehensive training for staff, will be essential to ensure consistency and accuracy in records, thereby minimizing measurement bias related to the reporting of nursing activity time. Finally, the implementation of ongoing evaluation and feedback mechanisms will further help identify and correct biases throughout the research process.

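### Nurse-estimated minutes enter nursing time and cost as fixed values, so time- and cost-based results look too certain, and the remedy in section 2.9 acts on records that hold no durations

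*Protocol article*

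**What the plan says.** Section 2.8 of the protocol article sets out the costing. The minutes come from nurses' own estimates: "Nursing time will be estimated using a convenience sample of nurses from the hospitals included in this study". It continues: "For each nursing activity, the participating nurses will indicate the average time spent on the activity and devices relevant to each intervention". A cost per minute, derived from annual salary, is then "multiplied by the amount of time spent on each nursing activity and by the total number of activities performed for each patient", and device prices are added. The article gives neither the number of nurses nor whether their averages are pooled over hospitals or formed within each hospital.

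The derived times go into t-tests, ANOVA, linear regression and quantile regression, which "will be performed to evaluate the possible variability in nursing time across hospitals and DRGs". Cost is the outcome in linear, logistic and quantile regression. On testing, section 2.8 says: "The level of significance for all analyses will be fixed at *p* < 0.05". The only sensitivity analyses it mentions vary the imputation models for missing nursing-record data.

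Section 2.9 expects data from all areas of Italy, "with an estimated sample size of at least 15,000 individuals". It names the nurse estimates as a possible source of over- or underestimated cost, and answers with guidelines and staff training "to ensure consistency and accuracy in records, thereby minimizing measurement bias related to the reporting of nursing activity time". Section 2.2 says what the records supply: "Nursing care activities (i.e., frequency and type) will be collected from nursing records". The nursing-record part of Table 1 lists number and type of activities, care complexity and nursing assessment, with no duration. By section 2.7 the records cover care given in 2022, and the study began in January 2024.

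**The concern.** An average over a sample of nurses has estimation error. Once it is multiplied into patients' costs, that error is the same for every patient costed with it. Standard errors computed from patient-to-patient spread cannot see it, and recruiting more patients does not reduce it. A DRG that relies heavily on an activity whose minutes are overestimated will look expensive, with a small p-value to match.

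This bears on the first primary aim (section 2.1), cost variability between and within DRGs. The Introduction suggests that results could inform DRG cost weights or a separate nursing intensity weight. The mitigation in section 2.9 is worded as if better records would improve the minutes, although the minutes do not come from the records.

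The point is estimation error in the mean minutes. Patient-to-patient variation in how long an activity takes is a different matter.

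**Working it through.** **1. The plan's own figure.** The 15,000 is an expected count with no effect size, SD or power behind it, so it can be neither reproduced nor refuted. It serves below only as N.

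**2. Structure.** Let patient i have n_ij performances of activity j, true mean minutes t_j, estimate t_j(1 + e_j), and cost per minute w.
- Error in mean cost = w Σ t_j e_j n̄_j. It depends on the mean counts n̄_j, not on N.
- Error in a contrast of DRGs A and B = w Σ t_j e_j (n̄_Aj − n̄_Bj). It vanishes if the two DRGs use activities identically.
- If e_j is the same for all activities, all times are rescaled by one factor. Test statistics and R² on time do not change; cost levels do.

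**3. Inputs.** From the article: N = 15,000 and a 5% level. Assumed, because not stated: m nurses per activity; J = 20 equally weighted activities; between-nurse CV 0.5; correlation ρ of a nurse's errors across activities, 0 to 0.3; patient CV of cost 0.5 to 1.0; one pooled time per activity.

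**4. Overall mean (relative SE).**
- Patient part = CV_patient/√N: 0.5/√15,000 = 0.41%; 1.0/√15,000 = 0.82%.
- Shared part = (CV_nurse/√m) × √((1 − ρ)/J + ρ). With m = 20 and ρ = 0: 0.1118 × √0.05 = 2.5%. With ρ = 0.3: 0.1118 × √0.335 = 6.5%.
- With 30 unequally used activities (effective J about 10) the same formula gives 0.1118 × √0.10 = 3.5% and 0.1118 × √0.37 = 6.8%.

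| Nurses (J = 20) | Shared part | Total SE / patient-only SE |
|---|---|---|
| 5 | 5.0–12.9% | 6.2–32 |
| 20 | 2.5–6.5% | 3.2–16 |
| 50 | 1.6–4.1% | 2.2–10 |

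**5. Mean cost of one DRG with 300 patients.** The patient part is now 2.9–5.8%. Coverage of a nominal 95% patient-only interval = 2Φ(1.96 × SE_patient/SE_total) − 1.

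| Nurses | SE ratio | Coverage |
|---|---|---|
| 5 | 1.32–4.59 | 86% down to 33% |
| 20 | 1.09–2.45 | 93% down to 58% |
| 50 | 1.04–1.73 | 94% down to 74% |

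**6. Contrast of two DRGs with equal true cost and different activity mix.** Simulation with J = 20, ρ = 0, nurse CV 0.5, log-SD 0.5 in activity mix, gamma patient frailty with CV 0.5, and 1,500 replicates. Rejection rate at a nominal 5%:

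| Patients per DRG | Times known | 5 nurses | 20 nurses | 50 nurses |
|---|---|---|---|---|
| 300 | about 5% | 15% | 9% | 6% |
| 1,500 | about 5% | 39% | 18% | 10% |

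A separate check with 30 activities and 20 nurses gave about 8–10% at 300 and 12–15% at 1,500, falling to 6–8% with 50 nurses. As an SE deficit, 9% corresponds to 1.96/1.695 = 1.16 and 18% to 1.96/1.341 = 1.46.

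**7. DRG share of variability.** In a simulation of 50 DRGs with 300 patients each (15,000 in all), R² was 0.050 with known times and ranged over 0.043–0.065 when the minutes came from 5 nurses. With 20 nurses it was 0.065 against 0.058–0.077. These ranges also include redrawn patients.

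**8. The remedy.** The records hold counts and types from 2022; the minutes come from a later survey of nurses. Training after January 2024 cannot alter those records, and more accurate counts would not correct the minutes.

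**The case against.** The strongest objection is that lack of propagation is inferred from silence. Section 2.8 never says that the minutes are treated as known, this is a condensed article, and an analysis plan not shown here could resample the nurses. That stands as a caution. But the article does fix the plug-in calculation and the tests that follow, and it does state a mitigation, which does not work as worded.

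On size, a reader might infer from the overall mean that DRG comparisons are also 3 to 16 times too certain. The calculations do not support that. The whole-sample mean is not one of the aims in section 2.1, and the inflation for DRG contrasts is far smaller. The upper end for the overall mean also depends on error common to all activities, which cancels in DRG tests on nursing time.

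On the remedy, section 2.9 openly discloses the risk, and its stated target is the reporting of activity time. Training can fairly be read as covering the nurses who give estimates. Even so, it would reduce bias and not sampling error.

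Finally, resampling a convenience sample captures neither its selection nor a misjudgement shared by all nurses. That is correct, and the revised text should say so.

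**Conclusion.** The concern holds in limited form. As written, nursing times and costs carry an error shared by all patients costed with the same mean minutes, and the stated analyses reflect patient sampling only. With 20 nurses and a between-nurse CV of about 50%, that error is about 2.5–7% of the overall mean, against under 1% from patient sampling. For DRG contrasts a nominal 5% test becomes roughly 8–10% at 300 patients per DRG and 12–18% at 1,500. With 50 nurses and small DRGs the effect is slight, and the DRG share of variability is little exposed. All these sizes rest on assumed nurse numbers, spread, activity mix and DRG sizes, none of which the article gives.

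Two stronger readings are not supported. A reader might infer that every result is affected, but the chi-square test on activity frequency and the objective on amount of nursing activity use no minutes. A reader might also infer that all 15,000 patients share one error. That requires pooled times, and the pooling rule is not stated. With hospital-specific times the error is shared within a hospital and mixed with the hospital differences that section 2.8 also tests.

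**What to change.** - Keep each nurse's individual estimates, and state the number of nurses and whether times are pooled or hospital-specific.
- For DRG-level cost, DRG and hospital contrasts, and the DRG share of variability, report intervals from a bootstrap that resamples nurses together with patients. Draw each nurse's whole set of minutes, so that correlation across activities is kept, and draw within hospital if times are hospital-specific. Report whether conclusions change.
- In section 2.9, replace the claim that training and accuracy in records minimise time-reporting bias. Say instead that the records are from 2022 and hold no durations, that sampling error in the minutes is carried into the intervals, and that bias shared by the nurses or due to their convenience selection remains.

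The cost is analysis wording and some computing time, since the estimates are to be collected anyway. The downside is wider intervals.

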## Abstract

**Background**: Rising costs and demands for improved quality of care present complex challenges for existing healthcare systems. The strain on healthcare resources is exacerbated by the increasing complexity of patient conditions. The Diagnosis-Related Group (DRG) system classifies inpatients according to clinical and treatment criteria, controls healthcare expenditures, and ensures the sustainability of procedures. The cost of nursing care is included in the DRG system in the same way as other fixed costs of hospital care, but the amount of nursing care provided for the same DRG can vary widely. This study, which is based on this protocol, will aim to assess the variability of nursing costs within and across DRGs and to measure how much variability in nursing care is explained by DRGs by comparing nursing care delivery in acute care hospitals with the DRG reimbursement system in Italy. It is necessary to develop a specific protocol to ensure systematic and consistent data collection at the national level. **Methods**: A multicenter retrospective cross-sectional study will be conducted. A random sample of five public Italian hospitals will be enrolled. Patients included in medical or surgical DRGs, hospitalized and discharged in 2022 will be included. Data will be collected retrospectively from two sources: hospital discharge records and nursing records. Inferential statistics will be used to assess the variability of nursing time and costs across hospitals and DRGs. Nursing costs will be determined by several factors, including time spent on nursing activities and the hourly wages of nursing staff. The time needed to complete each activity will be estimated by a convenience sample of nurses from the hospitals included in this study. The annual salary of nurses will be used to calculate the nursing cost per minute, multipled by the amount of time spent per each nursing activity. The cost per patient per day of hospitalization will be calculated. **Conclusions**: The results of this study will shed light on the variation in nursing care across different DRGs. This understanding will guide recommendations for optimizing healthcare resource allocation and enhancing the efficiency of the DRG system in Italy.

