### 2.3. Study Setting

A random sample of 5 public acute hospitals will be selected from the total number of potentially eligible hospitals that have expressed interest in participating in this study. To ensure representativeness across Italy, one hospital will be chosen from each geographical area identified according to the classification of the Italian National Institute of Statistics (ISTAT):Northwest (Liguria, Lombardia, Piemonte, and Valle d’Aosta);Northeast (Emilia-Romagna, Friuli-Venezia Giulia, Trentino-Alto Adige, and Veneto);Central (Lazio, Marche, Tuscany, and Umbria);South (Abruzzo, Basilicata, Calabria, Campania, Molise, and Puglia);Islands (Sicily and Sardegna).

To ensure randomization when selecting the sample of hospitals, a comprehensive list of all public hospitals that expressed interest in participating in this study across the five geographical areas of Italy will be created. Then, we will use stratified random sampling to randomly select one hospital from each area, employing a random number generator to eliminate bias.

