### 2.7. Procedures

This study started in January 2024 and is planned to end in March 2025. First, a pilot study was conducted to assess the characteristics of the EHR in the enrolled hospitals. Given the lack of a unique national electronic system for storing health information, heterogeneity in the collection and organization of the nursing activities is expected. Therefore, a preliminary meeting was organized with the nursing directors of each hospital. During this meeting, nursing directors described the EHR used in their hospitals. From this information, an electronic dataset was prepared to allow each hospital to enter information on nursing care activities. For each hospital, two medical and two surgical wards will be considered for enrolment. If there are more than two medical/surgical wards in the same department, the two wards with the highest number of patients admitted during the study period will be selected.

Eligible patients will be enrolled by searching the EHR. Data will be collected retrospectively to gather information on nursing care provided in 2022. This study will collect data from all patients included in medical or surgical DRGs. All nursing activities performed on these patients and documented in the EHR will be considered.

Within each hospital, a procedural manager will be designated to extract and de-identify data of interest. The data of patients who meet the inclusion criteria will be transmitted to the principal investigator (PI) by uploading the data into a secure server specific for this study. The upload will take place via a dedicated cloud platform established on an ad hoc basis for the project, allowing each local investigator of the participating centers to access and provide data.

For login purposes, each local investigator will have a username and password (which can be modified by the user after the initial login). Each local investigator will only have access to his or her own uploaded data, while the principal investigator will have access to all the data submitted by each participating center. The Italian Regulatory Board for Nursing Professions (FNOPI) owns the server where the data will be kept. Data gathering will be continuously evaluated, and all disaster recovery measures will be in place. Figure 1 summarizes the steps of the study.

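### Activity minutes come from a hospital-level convenience sample of nurses that is neither tied to the enrolled wards nor balanced across hospitals and ward types

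*Protocol article*

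**What the plan says.** Section 2.8 states the source of the minutes: "Nursing time will be estimated using a convenience sample of nurses from the hospitals included in this study". The Abstract repeats it: "The time needed to complete each activity will be estimated by a convenience sample of nurses from the hospitals included in this study". In section 2.8, "the participating nurses will indicate the average time spent on the activity and devices relevant to each intervention". The result goes straight into the cost: "This cost per minute will then be multiplied by the amount of time spent on each nursing activity", and by the number of activities performed for each patient. Wages come from national cost tables and device prices from a national list.

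The activity counts have a different source. Section 2.3 gives the hospitals: "A random sample of 5 public acute hospitals will be selected", one per geographical area. Section 2.7 gives the wards: "For each hospital, two medical and two surgical wards will be considered for enrolment". Where a department has more than two such wards, those with the most admissions are taken. The care is that of 2022. On timing, section 2.7 says: "This study started in January 2024 and is planned to end in March 2025".

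Section 2.9 names the nurse estimates as a source of bias: "This approach may not accurately capture the variability in nursing care across different settings". It accepts that costs may be over- or underestimated. In response it lists data-collection guidelines, staff training, and ongoing evaluation and feedback.

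**The concern.** Cost is a product of counts and minutes, and the two factors are drawn from different frames. The counts belong to selected wards in one calendar year. The minutes belong to whichever nurses of the hospital are convenient to ask. A nurse from a medical or surgical ward that was not enrolled fits the stated description as well as one from an enrolled ward. A sample mostly of medical-ward nurses, or mostly from one hospital, would also comply.

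The minutes decide how much a dressing change counts relative to, say, a drug administration. DRGs use activities in different proportions, so activity-specific errors in the minutes alter the cost differences between DRGs, which is the first primary aim in section 2.1. They can also alter the share of variability that DRGs explain, which is the second. Because the error comes from who is asked, more respondents recruited in the same way would not reduce it.

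**Working it through.** The plan gives no number of respondents, spread of answers or averaging rule for the nurse estimates, so it has no figure of its own to reproduce. Three checks are possible.

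**1. Number of wards.** 5 hospitals × (2 medical + 2 surgical) = 20 planned wards.

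**2. What kind of error matters.** Let patient *i* have n_ik activities of type *k*, each given t_k minutes, so that nursing time is T_i = Σ_k n_ik t_k.

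- Uniform error: if every t_k is multiplied by c, then T_i becomes cT_i. The between-DRG and total sums of squares are both multiplied by c², so their ratio is unchanged. This holds exactly for time and for labour cost. Device cost is added separately and does not scale with the minutes.
- Activity-specific error: if t_k is multiplied by a different c_k for each activity, the weights change and the ratio need not stay the same.

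A simulation on assumed values shows both cases. It had 15,000 patients, 50 DRGs and five activities of 5, 10, 15, 3 and 20 minutes.

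| Minutes used | Share of variance in time explained by DRG |
|---|---|
| True minutes | 0.156 |
| All × 1.3 | 0.156 |
| × 1.5, 0.7, 1.3, 1 and 0.6 by activity | 0.177 |

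The third row is one example. Its size and direction depend on the chosen values.

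**3. Shift in one activity's mean if one hospital dominates.** Assume that answers are pooled by respondent over all hospitals, that one hospital supplies share s of them, and that it reports r times the minutes of the other four. Relative to the equal-hospital mean:

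shift = (s·r + 1 − s) / (0.2·r + 0.8) − 1

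| s | r = 1.2 | r = 1.5 |
|---|---|---|
| 0.5 | 1.10/1.04 − 1 = 5.8% | 1.25/1.10 − 1 = 13.6% |
| 0.6 | 1.12/1.04 − 1 = 7.7% | 1.30/1.10 − 1 = 18.2% |
| 0.8 | 1.16/1.04 − 1 = 11.5% | 1.40/1.10 − 1 = 27.3% |

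With r = 1.3, shares of 0.4, 0.6 and 0.8 give 5.7%, 11.3% and 17.0%. At s = 0.2 the shift is zero. If the dominant hospital reports shorter times, the shift is downward: with r = 0.7 it is −6.4%, −12.8% and −19.1% for the same three shares.

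**4. If minutes are instead averaged per hospital.** Dominance by one hospital then disappears, but the mix of wards inside each hospital's sample remains. If one hospital's answers came mainly from surgical nurses and another's mainly from medical nurses, part of the difference in time and cost between them would reflect who answered.

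**The case against.** **Readings the text does not support.** A reader might infer that the minutes come from nurses other than those of the enrolled wards. The text does not say so: such nurses are neither required nor excluded. A reader might infer that the minutes describe 2024-25 practice. That timing is inferred from the study dates and the future tense, and no reference period is stated. A reader might infer that emergency, day-hospital or maternity nurses would be asked. Section 2.4 limits the study to medical and surgical departments and excludes those units, so the natural reading leaves them out. A reader might also infer that the largest supplier of respondents sets the minutes for everyone. That needs pooling by respondent, which no section states. Section 2.8 plans comparisons of nursing time across hospitals, so hospital-specific minutes remain possible.

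**A condensed article.** Quotas, survey wording and the averaging rule may stand in a full protocol or analysis plan that is not shown, and their absence here is not a fault. The point does not rest on it. It rests on the method that the article does state, twice: selection by convenience, with the hospital as frame.

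**Already disclosed.** Section 2.9 is open about the bias, and section 3 presents the study as descriptive. Both facts count in its favour. The listed measures, however, concern how nurses report and not which nurses report.

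**Weak magnitude.** The 6% to 27% is a shift in one activity's mean on assumed inputs. It does not measure the effect on the primary aims. The equal-hospital mean is also not the truth at any one hospital: with r = 1.5 it equals 1.1, which overstates four hospitals by 10% and understates the fifth by 1 − 1.1/1.5 = 27%. This stands, and it is why a single equal-weight mean is not enough as a remedy.

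**Conclusion.** The point holds in a limited form. The plan fixes a convenience sample at hospital level for the one unit input to cost that is taken from local opinion. It does not tie that sample to the 20 planned wards or balance it across hospitals and ward types. The minutes may therefore fail to represent the care being costed. Comparisons between DRGs and between hospitals can be biased where the error differs by activity. A uniform error would leave the DRG-explained share of nursing time as it is.

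The documents do not allow the size to be estimated. The 6% to 27% holds only under pooling by respondent, a 50-80% share from one hospital and a 1.2-1.5 ratio of minutes. The change from 0.156 to 0.177 shows that activity-specific error can move the explained share, and nothing about by how much it would do so here. This is a cheap improvement worth making before the nurse estimates are collected, and not a reason to doubt the design as a whole.

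**What to change.** - **Who is asked.** Replace the convenience sample with nurses from the enrolled wards, with the same quota for each ward. Prefer nurses who worked there in 2022 where they are available, without making this a condition.
- **How answers are combined.** Average within ward before combining, so that no ward or hospital dominates through its number of respondents.
- **Sensitivity analysis.** Re-cost all stays once with hospital-specific minutes and once with ward-type-specific minutes (medical or surgical). Report whether the cost differences between DRGs and the DRG-explained share change.
- **Section 2.9.** Add the choice of respondents to the listed measures, separately from guidelines and training.

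The cost is an eligibility line and a quota for a survey already planned, plus two repeat costings. The downsides are somewhat harder recruitment, chiefly in wards with high turnover since 2022, and some recall error if nurses are asked about 2022 practice.
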